### 3.2. Characteristics of the TAVI Operators

There must be at least one expert interventional cardiologist who has performed ≥ 30 TAVI/year as a first operator for at least 3 years and with regular experience in coronary revascularization procedures (more than 75 PCI/year), the use of endovascular devices, and percutaneous treatment of peripheral complications [33].

### 3.3. Sample Size

The sample size was calculated on the basis of previous studies. In the PARTNER cohort B trial, the patients were not considered to be suitable candidates for surgery after evaluation by a cardiologist and two cardiovascular surgeons. Patients that did not have significant comorbidities were enrolled as having prohibitive surgical risk if their STS score was 10% or higher. In this trial, the 30-day all-cause mortality in TAVI patients with prohibitive surgical risk (n = 179) was 5% [7]. In PARTNER cohort A, including 348 high-surgical-risk patients treated with TAVI, the rate of death from any cause was 3.4% at 30 days [8].

In the national US registry, 7710 patients were enrolled, including 1559 (20%) inoperable patients and 6151 (80%) with high-risk cases. Among the 3133 patients for whom 30-day outcome data were available, the incidence of death was 7.6% [29].

In an analysis of the prospective Austrian TAVI registry, 30-day mortality in high-risk and inoperable patients undergoing transfemoral TAVI was 6.2% in patients treated in hospitals with CS on site [30]. Unfortunately, updated 30-day mortality data for patients with prohibitive or high surgical risk are not available. The available literature data are summarized in Table 3.

According to these data, the mean 30-day mortality rate is 6.6%. The sample size will be 200 patients, which demonstrates the non-inferiority of the alternative treatment strategy compared to the standard of care with an alpha error of 5%. We considered a non-inferiority margin of 3%, such as to exclude mortality rates greater than 10% at the upper limit of the 90% confidence interval.

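### The 6.6% reference mortality matches a pool that counts the Austrian registry as 2 deaths in 290; at the printed rates of 6.2% or 6.9% the pool is about 7.0-7.1%

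*Protocol article*

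**What the plan says.** Section 3.3 (Sample Size) of the protocol article reviews four sources of 30-day mortality after TAVI in high-risk or inoperable patients, summarises them in Table 3, and concludes: "According to these data, the mean 30-day mortality rate is 6.6"%. For the Austrian registry the text says that mortality in patients "undergoing transfemoral TAVI was 6.2% in patients treated in hospitals with CS on site". Table 3 shows the same registry as 2/290 with a printed rate of 6.9%.

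The section then fixes the sample size, at a 5% level: "The sample size will be 200 patients, which demonstrates the non-inferiority of the alternative treatment strategy compared to the standard of care with an alpha". Further on it gives the criterion: "We considered a non-inferiority margin of 3%, such as to exclude mortality rates greater than 10% at the upper limit of the 90% confidence interval". No power is stated, and neither the averaging method nor the type of confidence interval is named.

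**The concern.** Three Austrian rates stand side by side: 0.69% (the printed count), 6.9% (the printed percentage) and 6.2% (the text). If the wrong one stayed in the table only, this would be a typographical slip. The question is whether it entered the 6.6%.

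That matters because the trial has a single arm. It has no concurrent control, and 6.6% is the rate that section 3.3 uses to represent the standard of care for this population in its non-inferiority claim. A reference rate that is too low makes N = 200 look better placed against the 10% ceiling than it is.

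**Working it through.** **Inputs** (Table 3 unless noted)

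| Source | Count | Rate from count | Rate printed |
|---|---|---|---|
| PARTNER, inoperable | 9/179 | 5.03% | 5.0% |
| PARTNER, high risk | 12/348 | 3.45% | 3.4% |
| US registry | 239/3133 | 7.63% | 7.6% |
| Austrian registry | 2/290 | 0.69% | 6.9% (text of section 3.3: 6.2%) |

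The first three rows are consistent to within rounding. In the fourth, 6.9% corresponds to 20/290 and 6.2% to 18/290, if 290 is the denominator in both cases.

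**Step 1: reproduce the plan's figure.** Patient-weighted mean = total deaths / total patients.

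- Patients: 179 + 348 + 3133 + 290 = 3950.
- Deaths with the printed counts: 9 + 12 + 239 + 2 = 262.
- 262/3950 = 6.63%, which rounds to the stated 6.6%.

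**Step 2: the same formula with the other Austrian figures.**

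- 18 deaths (6.2%): 278/3950 = 7.04%.
- 20 deaths (6.9%): 280/3950 = 7.09%.

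**Step 3: could another route give 6.6%?** The other three sources contribute 260 deaths. With 0, 1, 2 and 3 Austrian deaths the pool is 6.58%, 6.61%, 6.63% and 6.66%, so only 0 to 2 deaths round to 6.6%, and 2 is the only such count printed. With the Austrian rate at 6.2% or 6.9%, other averages give:

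| Method | Austrian 6.2% | Austrian 6.9% |
|---|---|---|
| Unweighted mean | 5.58% | 5.75% |
| Inverse variance, fixed effect | 6.68% | 6.73% |
| Random effects | 5.67% | 5.82% |
| Logit, fixed effect | 7.17% | 7.22% |
| Arcsine, fixed effect | 6.97% | 7.02% |
| Square-root-n weights | 6.32% | 6.44% |

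Leaving the Austrian registry out gives 260/3660 = 7.10%. None of these rounds to 6.6%.

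**Step 4: benchmark plus margin.** 6.6% + 3 = 9.6%. Corrected: 7.04% + 3 = 10.04% and 7.09% + 3 = 10.09%.

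**Step 5: upper limit for an estimate equal to the benchmark, n = 200.** Wald 90% limit = p + 1.645 × √(p(1−p)/200).

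- p = 6.6%: 6.60 + 2.89 = 9.49%.
- p = 7.04%: 7.04 + 2.98 = 10.02%.
- p = 7.09%: 7.09 + 2.99 = 10.08%.

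The corrected values are only just over 10%. Observed rates in 200 patients move in steps of 0.5 points: 14 deaths (7.0%) give a Wald limit of 9.97%, and 15 deaths (7.5%) give 10.56%.

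**Step 6: chance that the upper 90% limit is below 10%, n = 200.** The largest number of deaths that passes depends on the interval; the chance is the binomial probability of that many deaths or fewer.

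| Interval | Most deaths that pass (upper limit) | True rate 6.6% | True rate 7.1% |
|---|---|---|---|
| Exact | 12 (9.54%) | 44% | 33% |
| Wilson | 13 (9.99%) | 55% | 44% |
| Wald | 14 (9.97%) | 66% | 55% |

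The fall is about 11 points in each row.

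**The case against.** The strongest reply is that nothing operative moves. The 10% ceiling is printed as an absolute figure, N is fixed at 200, and the correction brings benchmark plus 3 points closer to that ceiling (10.0-10.1% against 9.6%). This stands, and it limits the severity.

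A reader might infer that the 3-point margin, or a planned probability of success, was derived from the faulty 6.6%. The document does not support this. Section 3.3 presents the margin as a choice without deriving it from 6.6%, and it states no power at all. The chances in step 6 are therefore consequences worked out here. They also depend on what is assumed about future patients: correcting a historical average does not change the mortality that the trial will observe. The modest chances at 6.6% exist already and are a separate matter.

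A reader might also take 7.0-7.1% as the established correct value. It is conditional. The text limits 6.2% to patients treated at sites with surgery, while Table 3 does not say whom its 290 patients represent, so 6.2% and 6.9% may describe different groups and the denominator is unverified.

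Nor is it proven that the count of 2 was used. The averaging method is not stated, and 0 or 1 deaths would also round to 6.6%. The inference is still strong, since 2 is printed and no other method tried reproduces the figure. A digit lost when the PDF was read does not explain it, because the 6.6% in the running text itself needs a count that low.

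Finally, Table 1 lists other 30-day mortality rates (for example 2.2% and 3.1%), so 6.6% is not the only mortality figure in the article. Those registries are not restricted to high-risk patients, and section 3.3 does not use them.

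**Conclusion.** The point holds as a numerical error in the reference rate. Table 3 contradicts itself and the text on the Austrian registry, and the stated 6.6% agrees with the erroneous count and not with either plausible rate. If n = 290 is right and the rate is 6.2% or 6.9%, the patient-weighted reference is 7.04% or 7.09%, which is 0.4-0.5 points above the stated value.

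The decision rule is unaffected: the 10% ceiling and N = 200 can stand. The planning picture does change. At 6.6% an estimate equal to the benchmark clears the ceiling by half a point on the Wald limit; at 7.04-7.09% it sits marginally above it. Should true mortality equal the corrected benchmark, the chance of meeting the criterion is about 11 points lower than at 6.6%, whichever of the three intervals is used. Severity: should-fix.

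**What to change.** 1. Check the Austrian numerator, denominator and patient group at source.
2. Correct the Table 3 cell, and reconcile the 6.2% in the text with the 6.9% in the table. If they refer to different groups, say so and state which one enters the mean.
3. Restate the reference rate as the patient-weighted mean of the verified counts, and name it as such. It will be about 7.0-7.1% if 290 is confirmed.
4. Name the interval method, and restate the operating characteristics of N = 200 against the unchanged 10% ceiling at the corrected rate.

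The cost is one source check, a corrected table cell and a few sentences. No patients are added and the success criterion stays as it is. The planning assumption becomes slightly less favourable.

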## 2. Methods and Analysis

### Study Design

“TAVI at Home” is a single-arm, interventional, multicenter, non-profit study conducted on patients with symptomatic and severe AS with an indication for TAVI through transfemoral arterial access in centers without on-site CS. The study is based on a single-arm design, aiming to evaluate the feasibility and safety of this strategy. The robustness of the data will be strengthened through a multicenter approach. The study was approved by the ethics committee of the Local Health Agency of Romagna (C.E.-ROM) and registered on ClinicalTrials.gov (NCT05886517) on the 2 of June 2023. Indication for TAVI will be given by the HT according to inclusion and exclusion criteria (Table 2). The cardiac surgeon is an important part of the HT; in particular, they are fully involved in the clinical and technical evaluation for proper patient selection. Surgical risk stratification will be performed on all patients using LogEuroSCORE, EuroSCORE II, and STS models for subgroup analysis. Eligibility will be clearly stated on the candidate’s personal record. The cardiac surgeon is requested to provide their opinion on the futility of ECS in the case of severe structural complications. A dedicated clinical interview, involving the clinical cardiologist, the interventional cardiologist, and the cardiac surgeon, will be planned to inform patients about their TAVI indication, the possibility of adhering to the experimental study, and to obtain a signed informed consent form. During the clinical interview, it will be clearly explained to the patient that in case of severe structural complications requiring ECS, the intervention will be deemed futile. 

The study will consist of two phases. A pilot phase enrolling 20 patients (10% of the total expected sample) will be conducted to assess the safety of the procedure. In this phase, a maximum of 4 adverse primary outcome events will be allowed based on the range of variability according to previous data [7,8,29,30].

The pilot phase of this study will be conducted at the Morgagni Hospital, Forlì. Once completed, an interim analysis will be performed by an independent data safety monitoring board. In the second phase, up to 10 centers will be involved to reach the final population of 200 patients. 

The study will be performed according to the Declaration of Helsinki and ICH Good Clinical Practice.

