## 3. Study Population

The study population will consists of patients over 75 years of age with severe symptomatic AS with an indication for TAVI. Eligibility will be determined based on a multidisciplinary discussion within the HT, an assessment of the prohibitive surgical risk according to the VARC consensus, or high surgical risk calculated by specific scores [31,32]. The exclusion criteria are contraindications for transfemoral access, aortic valve bioprosthetic dysfunction, bicuspid aortic valve, and instrumental characteristics, evaluated using CT angiography and associated with an increased risk of major complications. All inclusion and exclusion criteria are listed in detail in Table 2. Patients not fulfilling the inclusion criteria or meeting any exclusion criteria will follow the usual organizational pathway, thus undergoing TAVI in a center with CS. Figure 1 shows the study design.

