## Figures and Tables

**Figure 1 jcdd-12-00063-f001:**
[figure not shown]
Study scheme.

**Table 1 jcdd-12-00063-t001:** Conversion to emergent cardiac surgery and principal structural complications after TAVI in principal international registries [14,21,22,23,24]. # 30-day mortality; * in-hospital mortality; ^ 24 h mortality.

	Source (2007–2009)	Source 3 (2014–2015)	France 2 (2010–2012)	France (2013–2015)	Gary (2010–2015)	STS (2011–2019)
N.° of patients	1038	1947	4165	12,557	15,964	276,316
Mean age	81	81	83	83	81	81
LogES (%)	27	18	22	18	18	-
Death (%)	8.5 #	2.2 #	8.1 *	4.4 *	1 ^/5.2 *	2.0 */3.1 #
Conversion to open surgery (%)	2.7	0.6	1.2	0.5	1.3	0.6
Ring rapture (%)	-	0.2	0.3	0.4	0.4	-
Aortic dissection (%)	-	-	0.2	0.4	0.2	-
Coronary obstruction (%)	-	0.4	-	-	-	-
Cardiac tamponade (%)	-	-	1.3	2	1.0	-
Valve malposition (%)	0.3	-	1.3	1.1	-	-
2° Valve implantation (%)	-	0.7	2.3	1.8	-	-

**Table 2 jcdd-12-00063-t002:** Eligibility criteria.

Inclusion criteria - Severe symptomatic aortic valve stenosis - Age ≥ 75 years - Patients evaluated by Heart Team and selected on the basis of at least one of the following criteria: 1. High surgical risk (LogES > 20%, EuroSCORE II > 8%, and STS score > 8%) 2. Porcelain aorta 3. Hostile chest 4. Severe fragility 5. Severe liver disease/cirrhosis 6. Presence of a patent graft of an internal mammary artery crossing midline and/or adherent to the posterior table of the sternum 7. Severe pulmonary hypertension or severe right ventricular dysfunction - Feasible transfemoral access - Signed informed consent form
Exclusion criteria - Aortic valve bioprosthetic dysfunction - Bicuspid aortic valve - Anatomical features associated with an increased risk of major complications: 1. Severe left ventricle outflow tract or sub-annular calcification 2. Valvular ring to coronary ostia distance < 10 mm 3. Severe aortic root dilatation or out-of-range aortic annulus diameters for TAVI - Contraindication for femoral access

**Table 3 jcdd-12-00063-t003:** Thirty-day all-cause mortality after TAVI in patients with high or prohibitive surgical risk [7,8,29,30].

	Partner Trial		STS/ACCTVT Registry	Austrian Registry
	Inoperable	High-Risk	Inoperable + High-Risk	Inoperable + High-Risk
30 Days	(9/179) 5.0%	(12/348) 3.4%	(239/3133) 7.6%	(2/290) 6.9%

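### Section 3.3 claims non-inferiority to the standard of care, but a single arm set against a 10% ceiling from older cohorts can only test a historical performance goal

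*Protocol article*

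**What the plan says.** The section Study Design describes the trial this way: "The study is based on a single-arm design, aiming to evaluate the feasibility and safety of this strategy". There is no concurrent control group.

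Section 3.3 goes further: "The sample size will be 200 patients, which demonstrates the non-inferiority of the alternative treatment strategy compared to the standard of care". The comparator comes from the four cohorts of Table 3: "According to these data, the mean 30-day mortality rate is 6.6" per cent. The rule follows: "We considered a non-inferiority margin of 3" percentage points, so as to "exclude mortality rates greater than 10% at the upper limit of the 90% confidence interval". Section 3.3 also acknowledges that no updated 30-day mortality exists for patients at high or prohibitive surgical risk.

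Eligibility is narrower than surgical risk alone. Section 3 lists among the exclusions "instrumental characteristics, evaluated using CT angiography and associated with an increased risk of major complications", and Table 2 repeats this as "Anatomical features associated with an increased risk of major complications": severe outflow-tract or sub-annular calcification, coronary ostia less than 10 mm from the annulus, severe root dilatation, and annulus size out of range. Bicuspid valves, failed bioprostheses and unsuitable femoral access are also excluded. Section 3 sends patients who do not qualify to centres with cardiac surgery.

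**The concern.** Non-inferiority to the standard of care is a comparative statement: these patients do no worse without on-site surgery than they would do with it. A single arm can support that only if the external rate stands for what the same kind of patient would experience today in a Heart Valve Center. Two features of the document undermine this.

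- **Selection.** The protocol removes anatomy that, by its own account, raises the risk of major complications. Those are the complications for which on-site surgery would matter. Table 3 and section 3.3 describe no such exclusions for any benchmark cohort, and only the Austrian figure is described as transfemoral.
- **Era.** The introduction argues that complications have fallen markedly with newer technology and experience, yet the benchmark keeps older rates and treats them as the standard of care.

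As far as the documents show, both differences favour a pass. If the wording stands, a pass could be cited as showing that on-site surgery makes no difference, when selection and era could account for the result.

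**Working it through.** **Inputs.** n = 200, benchmark 6.6%, margin 3 points, ceiling 10%, 90% interval (section 3.3). Benchmark counts: 9/179, 12/348, 239/3133 and 2/290 (Table 3). Registry mortality and mean LogES: Table 1.

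**1. The plan's own benchmark.** (9 + 12 + 239 + 2)/(179 + 348 + 3133 + 290) = 262/3950 = 6.63%. This reproduces 6.6%, but only with the printed Austrian count of 2/290. That count conflicts with the 6.9% printed beside it and with the 6.2% in the text. This is a separate matter to reconcile. The US registry supplies 3133/3950 = 79% of the pooled patients, at 7.6%.

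**2. The plan's own interval.** An observed 6.6% in 200 gives a Wald 90% upper limit of 0.066 + 1.645 × √(0.066 × 0.934/200) = 9.49%. This is below 10%, so the stated condition is met at the benchmark rate.

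**3. Deaths allowed.** Section 3.3 does not name the interval method, so three are shown. Each row gives the largest number of deaths in 200 with an upper limit of at most 10%.

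| Interval | Most deaths | Observed rate | Upper limit | Upper limit with one more death |
|---|---|---|---|---|
| Clopper–Pearson | 12 | 6.0% | 9.54% | 10.14% |
| Wilson | 13 | 6.5% | 9.99% | 10.58% |
| Wald | 14 | 7.0% | 9.97% | 10.56% |

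**4. Probability of passing.** P(X ≤ 12) and P(X ≤ 14) for X ~ Binomial(200, p):

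| True 30-day mortality p | Exact rule (≤ 12) | Wald rule (≤ 14) |
|---|---|---|
| 4.4% (2 × 2.2%, SOURCE 3) | 90% | 97% |
| 6.2% (2 × 3.1%, STS) | 53% | 74% |
| 6.6% (the benchmark; also 3 × 2.2%) | 44% | 66% |
| 6.8% (2 × 3.4%, PARTNER high-risk) | 39% | 61% |
| 9.3% (3 × 3.1%) | 6% | 16% |
| 10.0% (the ceiling) | 3% | 9% |

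The last row shows that the rule works roughly as a one-sided 5% test against 10%. It is conservative with the exact interval and somewhat liberal with Wald. That is what the design delivers.

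**5. What Table 1 can and cannot add.** Thirty-day mortality is 8.5% in SOURCE (2007–2009) and 2.2% in SOURCE 3 (2014–2015). It is 3.1% in STS (2011–2019). In-hospital mortality is 8.1% in France 2 and 4.4% in France. Mean LogES fell over the same steps, from 27 to 18 and from 22 to 18, and none is given for STS. Calendar time and case-mix therefore moved together, and none of these registries is described as restricted to high-risk patients. The rates are context, not a replacement benchmark.

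**The case against.** **The multiple.** A reader might infer that the trial could declare success at two to three times current mortality. The documents do not support this as a finding. Trial patients must meet a high-risk score or another listed Heart Team criterion, while the lower rates in Table 1 come from registries not described as high-risk. LogES fell together with mortality, and section 3.3 says updated high-risk rates are unavailable. Three times is plausible only against the lowest figure, 2.2%. Three times 3.1% would pass just 6–16% of the time. This part of the objection stands, and no multiple is claimed here.

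**Selection in the benchmark.** The absence of anatomical exclusions in the description of the cohorts is silence in a condensed article, so the size of the mismatch is unknown. The Austrian cohort is transfemoral, high-risk or inoperable, and treated with surgery on site, so it matches on access and risk. The entry criteria other than the risk scores do not show a mismatch either, because the inoperable PARTNER cohort was also selected by clinical judgement. All of this stands. It limits how large the bias can be said to be, but does not supply the comparability that a non-inferiority claim needs.

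**The rest of the document is modest.** The aim and the design speak of feasibility and safety, the Conclusions make no non-inferiority claim, and the operative rule is already a fixed 10% ceiling. This is correct. It confines the fault to the wording of section 3.3 and lowers its severity.

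**No updated data exist.** That is a fair reason to adopt a historical performance goal. It is not a reason to call that goal the standard of care.

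**Conclusion.** The concern holds as a matter of what the trial can conclude. Section 3.3 attributes to the design a property it lacks. A single arm judged against 10% can show that 30-day mortality in a selected group lies below a historical ceiling. It cannot show non-inferiority to current care with on-site surgery, because selection and era cannot be separated from the effect of the setting.

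The rule admits 12 to 14 deaths in 200 (6.0–7.0%). Within the benchmark's own high-risk cohorts, a true rate twice PARTNER's 3.4% would pass 39–61% of the time. A true 6.2%, twice the STS rate, would pass 53–74% of the time.

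These probabilities assume independent binomial outcomes in 200 evaluable patients. The ranges reflect the unnamed interval method. The multiples are illustrations only, since the current rate for patients meeting Table 2 cannot be fixed from the documents. Severity: should be fixed. The decision rule and sample size need not change on this account.

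**What to change.** 1. In section 3.3, replace the non-inferiority wording with: *tests whether 30-day mortality in anatomically selected, transfemoral, high- or prohibitive-risk patients is below a historical performance goal of 10%.*
2. Limit the trial's stated conclusion to that sentence.
3. Beside the result, print the 30-day rates of Table 1 (SOURCE 3 2.2%, STS 3.1%). Note that these registries are not described as high-risk and that mean LogES fell together with mortality where it is reported.
4. Optional: a supportive comparison with earlier Heart Valve Center cases of the participating teams that meet the Table 2 criteria. Section 3.1 requires more than 36 TAVI a year there, so cases should exist.

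Items 1–3 change text only and need no further patients; their price is a weaker headline claim. Item 4 needs retrospective data collection, and the point does not depend on it.

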### 3.5. Outcome Measures

The primary endpoint will be 30-day all-cause mortality, which will be measured as the number of deaths within 30 days of the procedure. Secondary endpoints will include the assessment of technical success and the evaluation of single complications at 30 days after the procedure [32]. Technical success will be defined according to VARC-3 consensus [32]:-Freedom from mortality.-Successful access, delivery of devices, and retrieval of the delivery system.-Correct positioning of a single prosthetic heart valve into the proper anatomical location.-Freedom from surgery or intervention related to the device (excluding pacemaker implantation) or to a major vascular, access-related, or cardiac structural complication.

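### The claim that 200 patients demonstrate non-inferiority is unsupported: at the 6.6% benchmark the protocol's criterion is met only 44% to 66% of the time, depending on the interval method

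*Protocol article*

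**What the plan says.** The design is single-arm (Study Design: "The study is based on a single-arm design, aiming to evaluate the feasibility and safety of this strategy"), and the primary endpoint is a simple proportion (section 3.5: "The primary endpoint will be 30-day all-cause mortality, which will be measured as the number of deaths within 30 days of the procedure").

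Section 3.3 (Sample Size) reviews earlier TAVI cohorts and concludes "According to these data, the mean 30-day mortality rate is 6.6" percent. It then makes the claim at issue: "The sample size will be 200 patients, which demonstrates the non-inferiority of the alternative treatment strategy compared to the standard of care". The same sentence sets alpha at 5%. The margin follows ("We considered a non-inferiority margin of 3" percentage points), with the criterion worded as "such as to exclude mortality rates greater than 10% at the upper limit of the 90% confidence interval".

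The section gives no power and does not name the interval method. It gives no expected mortality for this trial separate from the 6.6% benchmark.

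**The concern.** The sentence presents non-inferiority as something that 200 patients deliver. A sample size only gives a probability of meeting a criterion, and that probability depends on the true rate and on the interval used. The section supplies enough inputs to work it out, and the answer is far from assured.

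This concerns the single primary endpoint of a study meant to inform whether TAVI can be done without on-site cardiac surgery. Readers, and the board that oversees the trial, would take from the sentence that a strategy performing at the benchmark will pass. At the benchmark, the result is in fact close to a coin toss. The unnamed interval method also matters: the choice moves the permitted number of deaths from 12 to 14 and decides whether the stated alpha holds.

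**Working it through.** **Inputs, all from section 3.3:** n = 200; benchmark mortality p = 6.6%; alpha 5%; upper limit of a 90% interval to lie below 10%. The upper limit of a 90% interval corresponds to a one-sided 5% test. The 3-point margin gives 6.6% + 3% = 9.6%, slightly below the 10% ceiling.

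**Step 1. Can the figure of 200 be reproduced?** The article shows no formula. A precision calculation for a 90% half-width of 3 points gives n = 1.645² × 0.066 × 0.934 / 0.03² = 185.3, so 186. At n = 200 and an observed rate of exactly 6.6%, the Wald upper limit is 0.066 + 1.645 × √(0.066 × 0.934 / 200) = 9.49%, which lies below 10%. So 200 is compatible with a calculation that treats the observed rate as equal to the planned rate. This is only a possible explanation: 186 is not 200, and nothing below depends on it.

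**Step 2. How many deaths are allowed?** Upper limits of the 90% interval for x deaths out of 200:

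| Deaths | Exact (Clopper-Pearson) | Wilson | Wald |
|---|---|---|---|
| 12 | 9.54% | 9.39% | 8.76% |
| 13 | 10.14% | 9.99% | 9.37% |
| 14 | 10.73% | 10.58% | 9.97% |
| 15 | 11.31% | 11.16% | 10.56% |

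Against the 10% ceiling the largest passing counts are 12 (exact), 13 (Wilson) and 14 (Wald). The expected count at 6.6% is 200 × 0.066 = 13.2, so under the exact interval a result of 13 deaths, about the expected one, already fails.

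**Step 3. Chance of success and true error.** With X binomial (200, p), the chance of success is P(X ≤ c):

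| Rule | c | p = 6.6% | p = 5.0% | One-sided error at p = 10% |
|---|---|---|---|---|
| Exact | 12 | 43.7% | 79.6% | 3.2% |
| Wilson | 13 | 55.0% | 87.0% | 5.7% |
| Wald | 14 | 65.7% | 92.2% | 9.3% |

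For the exact rule at p = 4.0%, P(X ≤ 12) = 94.0%.

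**Step 4. Sensitivity to the limit.** With 9.6% in place of 10%, the exact and Wilson rules both allow 12 deaths (43.7% at p = 6.6%) and Wald allows 13 (55.0%). The stricter limit does not help.

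**Step 5. Scale of the gap.** Under the exact rule with the 10% ceiling and p = 6.6%, a success probability of 80% is first reached at n = 413 (at most 31 deaths, 80.2%). Because the binomial is discrete, it stays at or above 80% only from n = 459.

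**The case against.** **No power is stated, and this is a condensed article.** The full protocol or analysis plan may give the power, the interval method and the expected rate. This stands in part: their absence here is no error, and the documents do not support saying that a stated power is wrong. But section 3.3 makes a positive statement about what 200 patients achieve, and its own inputs do not bear it out at 6.6%, whatever another document adds.

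**The result depends on the interval.** This stands. A reader might infer that a strategy performing at the benchmark will more likely than not fail. That is true for the exact interval (44%) but not for Wilson (55%) or Wald (66%), and the article does not choose between them. The supportable headline is the range.

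**The 6.6% is a benchmark from earlier studies, not a declared expectation.** This is fair. Table 2 excludes anatomy linked to major complications, and Table 1 shows 30-day mortality of 2.2% and 3.1% in later registries, though the article does not present those as restricted to high-risk patients. At a true 5% the chance is 80% to 92%. However, section 3.3 offers no other planning rate and says that updated figures for this risk group are not available. Setting the expected rate equal to the benchmark is the usual reading of a non-inferiority plan.

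**The aim is feasibility and safety.** This is true of the Study Design section, but section 3.3 still attaches a formal non-inferiority claim to the sample size.

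**Conclusion.** The concern holds in this form: the statement that 200 patients demonstrate non-inferiority is unsupported. If true 30-day mortality is 6.6%, the stated criterion is met 44% (exact), 55% (Wilson) or 66% (Wald) of the time, and each is well short of 80%. Only the exact rule keeps the one-sided error at 10% mortality within the stated 5% (3.2%, against 5.7% and 9.3%).

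The result assumes a binomial count in 200 evaluable patients, a true rate equal to the benchmark, and a reading of the 90% interval as a one-sided 5% test. At a true rate of about 5% or lower the design is reasonable: 80% under the exact rule at 5.0%.

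Two stronger readings are not supported. The article does not show that 200 came from a precision calculation; that is a guess that fits only roughly. Nor does a low chance of success mean that a missed criterion would be evidence of harm. It would mean only that mortality above 10% had not been excluded.

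**What to change.** Keep 200 patients and replace the sentence in section 3.3 with wording such as:

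> With 200 patients the goal is met if 12 or fewer deaths occur within 30 days (exact one-sided 95% upper limit <10%; actual alpha 3.2%). The probability of meeting it is 44%, 80% and 94% if true 30-day mortality is 6.6%, 5.0% and 4.0%.

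Add one sentence saying which mortality the sponsor expects in this selected population, and why.

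The cost is wording only: no extra patients and no change to the endpoint or to care. The drawback is that the figure at 6.6% looks less favourable than the present text. If the sponsor does expect 6.6% and wants 80% under the exact rule, wording alone will not achieve it, since that level is first reached at 413 patients.
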